### Exposure and Health Outcome Measures

In the pilot study, both exposure and health outcomes will be measured. Moreover, all workers will fill in the standardized questionnaire to provide sociodemographic, occupational, life-style, and health data. Biological sampling is planned twice a day (pre-and post-shift), while exposure to PM and other pollutants possibly present in subway will be measured over the working shift. Table 1 summarizes all airborne exposure measurements, while Table 2 summarizes exposure and effect biomarkers, biological matrices and corresponding chemical analysis required. We will use Turbo-DECCS - Medivac device for EBC collection (20 minutes), Tedlar bags with Medivac vial for exhaled air collection (2 minutes), urine sampling kits for urine collection (< 5 minutes). The pilot study is scheduled for six consecutive weeks, to allow a two-week follow up for every occupation. Three workers with the same occupation will be received at the same time an hour before their work-shift. During this time, the participant will undergo a medical check including spirometry and the biological sample collection, as depicted in Fig. 1. At the end of the medical check, the workers will be provided with the air sampling pumps and direct-reading devices for monitoring airborne exposure during their working-shift. After the working-shift, participants are received again for the post-shift medical check including spirometry and biological sample collection. All spirometry tests will be performed without bronchodilation by the same trained nurse. This standardized sequence of collecting samples, taking measurements and recording data is repeated for every worker daily for two weeks. It is worth mentioning that personal air samples will be taken over the entire workday, including periods of service and breaks. A laboratory technician assigned to each participant will wear all personal sampling pumps and devices because the participants themselves are not allowed to wear any devices that can potentially interfere with their job. Moreover, each technician will fill in the workers’ activity logbook to document all its tasks, their duration, and the place of their realization during each work-shift. These logbooks will thus provide contextual information for linkage with personal exposure measurement data.

**Table 1 Tab1:** Indoor air exposure measurements performed in the longitudinal pilot study in a Parisian subway

Outcome measured	Aerosol fraction	Type of measurement	Sampling method (pump and filter/head)		Sampling duration	Analytical method
Fine particle mass concentration	Inhalable (PM_10_, PM_2.5_)	Personal	3 pumps at 4 L/min	Teflon filter	8 h	Gravimetry (weighs before and after)
Metals (Fe, Cr, Cd, Al, Ba, Ni, Zn, Cu, Pb, Sb, Mn, As) mass concentration	Inhalable (PM_10_ and PM_2.5_))	Personal	2 pumps 2 L/min	Quartz filter	8 h	The metals present in particles are collected on a filter with a diameter varying from 47 to 150 mm, then dissolved in an acidic medium using a microwave mineralizer (closed system). The liquid sample is then diluted and analyzed by ICP-MS
Organic carbon/elemental carbon mass concentration	Respiratory (PM_4_)	Personal	1 pumps 2 L/min	Quartz filter - cassettes and cyclones + GALVIN (sealing filter for the cassette)	8 h	The analytical technique includes thermo-optical processes for the separate determination of EC/OC contents, based on the successive and controlled combustion of the different particles deposited on the filters, according to a given temperature program, with optical correction of scale deposits.
Monocyclic Aromatic Hydrocarbons	Gaseos	Personal	1–2 pocket pumps 0,2 L/min	Activated charcoal	8 h	(Benzene, Xylene (m, o, p), Toluene, 1,2,4 TMB)
Oxidative potential	Inhalable particles and gaseous	Personal	1 pump 2 L/min	Teflon filter (and storage cassette) + XAD2 adsorbent	8 h	1) immersion of the filter in Fox 2) chemical desorption in dichloromethane - solvent evaporation - recovery in DMSO - injection in FOX
Ultrafine particle count, size and LDSA	Respirable (PM_0.1_ (10 nm–300 nm))	Personal & stationary	5 DISCmini	impaction head	6-8 h	DISCmini, a portable personal direct-reading exposure monitor with a time resolution of 1 s.
Particle morphology and elemental composition	Respirable (PM_1_ and PM_0.1_)	Personal	1 pump 0.2 L/min	1 mini-Sampler (holding head) + grid filter (SEM)	10 min	Scanning electronic microscopy coupled with EDX (diffraction and impaction of x-rays on particles)
Fine and ultrafine particle mass concentration	PM_10_, PM_2.5_, PM_1_ (300 nm-32 μm)	Personal	1 GRIMM	Impaction head	8 h	Direct-reading optical particles counter Grimm 1.109, 31 channels, with a time resolution of 10s.
Volatile organic compounds		Stationary			8 h	Direct-reading device Gasmet
Hygrometry and temperature		Personal & stationary	2 Ecolog (ELPRO®)		8 h	Direct-reading device Ecolog (ELPRO®)

**Table 2 Tab2:** Biomarker measures performed in the longitudinal pilot study in the Parisan subway

Outcome measured	Biological matrix	Analytical method

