### Research Setting and Participants

The research will be conducted in a Parisian urban transport company in France for the experimental part and at Unisanté in Switzerland for the analytical part. The study samples will comprise three categories of underground subway workers: locomotive operators, security guards, and station agents in charge of information, ticket sale and control. All these professionals have their workstations underground. These jobs are considered the most exposed to PM compared to other professionals working outdoor, such as bus or tram drivers, controllers and administrative staff. They are also less concerned with other chemical exposure compared to maintenance workers.

The pilot longitudinal study will use a convenience sample of nine workers; three workers per occupation. Both women and men aged 40+, and non-smokers for at least 10 years (to avoid interference of smoking with the exposure-biomarkers-health outcome relationships) will be considered eligible. The only exclusion criteria are a counter-indication of spirometry test and acute or chronic morbidities other than COPD. The participants will have their workstations on subway line 7. This line is entirely underground, deep, has no mechanical ventilation and therefore represents one of the worst case scenarios in terms of exposure and one of the best for setting a pilot study. It offers a possibility to set up rooms for participant reception, biological sampling and equipment storage. The workers recruitment will be managed by the medical coordinator of the study. The medical coordinator will organise internal company meetings with workers, their supervisors and occupational physicians. At these meetings, workers will be informed on the objectives of the pilot study, inclusion criteria and invited to contact their occupational physician to declare their wish to participate in the study and to arrange an individual interview for this purpose. The occupational physicians will check the inclusion and exclusion criteria and collect the signed written informed consent form eligible workers. The recruitment of workers will be carried out in chronological order: The eligible workers who volunteer first will be given priority.

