### Statistical Analysis

Data collected within the pilot study will be analyzed using an exploratory approach. Descriptive analysis will give information on the cumulative trends of exposures to different PM fractions, their metal content and other airborne chemicals. Direct-reading fine and ultrafine particle exposure measurement data (from DISCmini and Grimm, Table 1) will be analyzed along with data from the activity logbooks, using time series analytical technics such as Bayesian spline analysis to get insights on the exposure sources and determinants.

Repeated data will be analyzed using mixed linear models and interval regression models for the censured data (below LOD/LOQ). Air and biomarker concentrations will be compared between occupations, using daily, pre- and post-shift log-transformed mean values with and without adjustment for variables collected through the standardized questionnaire (e.g., age, average home-to-work commute time, anti-oxidant diet, non-occupational exposure to PM). Correlation between external and internal exposure (based on urine and EBC biomarkers of exposure), internal exposure and early effect biomarkers, and the latter with FEV1/FVC will be tested, using post-shift to pre-shift values ratios for each biomarker. Analysis will be conducted applying different lag-times on the exposure estimates (e.g., 6 h, 14 h, and 24 h) to explore the temporal variation in biomarker levels. The most informative biomarkers (i.e., correlated both with exposure and particularly with FEV1/FVC ratio) will be selected for the field study.

In the field study, the central research hypothesis is that a panel of oxidative stress biomarkers measured in non-invasive samples, including OPEA will be more efficient for COPD diagnosis than single biomarker analysis. This hypothesis will be tested using generalized linear models. Besides, additional associations between dependent variables and explanatory variables will be examined, as shown in Fig. 3. Data management and statistical analyses will be performed using Stata, version 16, software.

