The constraints of our pilot study protocol entailed a very intensive field data collection from no more than nine participants, with one physician, one nurse, two PhD students, and a support team of five technicians present in the companies over six weeks. Given the diversity of exposure metrics and measurements and devices available it was hardly possible to include more participants. This drawback of the very complete exposure assessment in the pilot study, will be compensated with a large probabilistic sample in the field study. The latter is expected to have 90% statistical power to discriminate COPD cases from controls based on a quite small OPEA difference. On the other hand, a possible lack of power induced by the relatively small number of workers included in the pilot study will be compensated for by the exposure variance when including both highly exposed and less exposed workers, such as locomotive operators and station agents, respectively. It is noteworthy that the repeated measure design (twenty measurements per participant for urine and EBC) will contribute to increase the power of detecting short-term effects.

Bacterial contamination and endotoxin measurements were not included in the protocol due to limited resources, but also because these exposures do not raise any particular concern at the company. However, the COVID-19 pandemic has strongly affected the working conditions of subway professionals and possibly the respiratory health of those who have contracted this disease. If the pandemic continues, then this situation is likely to be an issue for a timely start and progress with the field study. To guaranty the participant and staff safety, the planning and logistics of worker medical checks should be revised. This may delay the sample and data collection process, but also decrease the participation rate. Indeed, additional time, equipment and human resources will make the field study more expensive.

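### In the pilot each occupation is followed in its own fortnight, so the planned comparison of air and biomarker levels between occupations is fully aliased with calendar period.

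*Protocol article*

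**What the plan says.** All references are to the protocol article.

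- **Sample** (Research Setting and Participants): "The pilot longitudinal study will use a convenience sample of nine workers; three workers per occupation".
- **Schedule** (Exposure and Health Outcome Measures): "The pilot study is scheduled for six consecutive weeks, to allow a two-week follow up for every occupation". Also: "Three workers with the same occupation will be received at the same time an hour before their work-shift". The daily sequence of samples and measurements "is repeated for every worker daily for two weeks".
- **Analysis** (Statistical Analysis): "Air and biomarker concentrations will be compared between occupations, using daily, pre- and post-shift log-transformed mean values with and without adjustment". The adjustment variables come from the questionnaire, and the examples given are "age, average home-to-work commute time, anti-oxidant diet, non-occupational exposure to PM". The same section calls the pilot analysis exploratory. It bases the correlations used to choose biomarkers on post-shift to pre-shift ratios, with several exposure lags.
- **Discussion**: a possible lack of power from the small number of pilot workers "will be compensated for by the exposure variance when including both highly exposed and less exposed workers", with locomotive operators and station agents as the examples. Repeated measurement, twenty per participant for urine and EBC, is cited as a further help.

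**The concern.** If all workers of one occupation are measured in one fortnight, and no other occupation is measured then, anything that shifts levels from one fortnight to the next appears in the data as a difference between occupations. Outdoor PM, weather and traffic are obvious candidates, and they may differ across six weeks. None of the example covariates is a calendar, weather or same-day background measure. Non-occupational PM exposure comes nearest, but as listed it is a questionnaire item and not a daily reading.

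What is at stake is the meaning of one planned output. A difference reported between station agents, security guards and locomotive operators could be a difference between three fortnights. The article does not mention this, although its Discussion does discuss the pilot's limitations.

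**Working it through.** **1. Reproduce the schedule.** 3 occupations × 2 weeks = 6 weeks, the stated duration. This holds only if the occupations run one after another. Staffing agrees: one technician accompanies each participant (Exposure and Health Outcome Measures) and there are five technicians (Discussion), so nine workers cannot be followed at once. Assuming five shifts a week, 10 shifts × 2 samples = 20 per worker, which matches the Discussion. In all, 9 workers × 10 shifts = 90 worker-shifts.

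**2. Can occupation be separated from period?** Rank of the design matrix over the 90 worker-shifts:

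| Model | Columns | Rank |
|---|---|---|
| Intercept + occupation | 3 | 3 |
| Intercept + occupation + fortnight | 5 | 3 |
| Intercept + calendar day + occupation | 32 | 30 |

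Adding fortnight adds nothing to the rank, so the two factors are the same factor. With day in the model, no occupation contrast is estimable. A straight-line time trend can be fitted, but only by extrapolating from one fortnight to another. It multiplies the variance of the occupation contrast by 3.0 for adjacent fortnights and 9.1 for the first against the third. For comparison, with one worker of each occupation in each fortnight the second model would have rank 5 of 5.

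**3. How large could the effect be?** The article gives no variance components, so these are assumptions on the log scale: worker SD s = 0.2 or 0.3, day SD 0.4, 10 shifts per worker, no true occupation effect, and fortnight SD τ = 0.05, 0.1 or 0.2.

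- Variance of a worker's mean: v = s² + 0.4²/10 = s² + 0.016. This is 0.056 for s = 0.2 and 0.106 for s = 0.3.
- Degrees of freedom of the occupation F-test on nine worker means: 3 − 1 = 2 and 9 − 3 = 6. The 5% critical value is 5.143.
- With fortnight effects, F is inflated by k = (v + 3τ²)/v.
- Rejection probability: P(F(2,6) > 5.143/k) = (1 + 5.143/(3k))⁻³.

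| τ | k, s = 0.2 | Rejects | k, s = 0.3 | Rejects |
|---|---|---|---|---|
| 0 | 1.00 | 5.0% | 1.00 | 5.0% |
| 0.05 | 1.13 | 6.3% | 1.07 | 5.7% |
| 0.1 | 1.54 | 10.5% | 1.28 | 7.8% |
| 0.2 | 3.14 | 27.1% | 2.13 | 17.0% |

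Worked example: τ = 0.2 and s = 0.3 give k = (0.106 + 0.12)/0.106 = 2.13, and 5.143/2.132 = 2.41. Then (1 + 2.41/3)⁻³ = 0.170.

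**4. Which stationary readings could help?** Table 1 marks stationary measurement for ultrafine particles, volatile organic compounds, and temperature and humidity. PM10 and PM2.5 mass, metals, organic and elemental carbon, and oxidative potential are listed as personal only.

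**The case against.** The strongest reply is that the occupation contrast is not what the pilot is for. None of its four stated aims is to compare occupations, and its analysis is declared exploratory. Biomarkers are selected on their correlation with exposure and FEV1/FVC, using post-/pre-shift ratios. Such ratios cancel any level shared by a worker's two samples on the same day. This stands: the selection of biomarkers is largely protected, which limits how serious the point is. It does not rescue the occupation comparison, which the article plans explicitly.

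Three stronger readings are tempting, and the article does not support them.

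- *Prevention will be aimed at the wrong occupation.* A reader might infer this because the Discussion links the three job types to prevention. There, however, the targeting rests on the exposure determinants in the activity logbooks, to be analysed with direct-reading data, and not on the comparison of occupation means.
- *Instrument drift or assay batch differs by occupation.* Nothing says that samples are assayed by fortnight or that instruments drift.
- *The Discussion's compensation statement is simply wrong.* It concerns the spread of measured exposure, and a wider spread does add information on an exposure-biomarker slope. But the part of the spread that lies between occupations also lies between fortnights, so a pooled slope that draws on it may be confounded. The statement needs a qualification, not deletion.

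The number of covariates and the choice of small-sample degrees of freedom can be left to the analysis plan and are not part of this point. The aliasing cannot be left to it, because it is fixed by the schedule.

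**Conclusion.** The point holds for the between-occupation comparison of levels, and for any pooled exposure-biomarker slope that uses variation between occupations. The aliasing follows from the stated schedule and needs no assumption about variances.

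The size of the resulting bias is not known. The false-positive rates of about 6%, 8 to 11% and 17 to 27% depend on the assumed fortnight SDs of 0.05, 0.1 and 0.2 and on the other assumed components. They show a range from negligible to material and do not estimate what happened in this pilot. Within-worker analyses are largely unaffected. For an exploratory pilot this is a correction worth making to the analysis and interpretation. It does not invalidate the pilot.

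**What to change.** The article reports that the pilot began in October 2019 and that some statistical analysis has started, so the change is to analysis and wording, not to the schedule.

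1. In Statistical Analysis, label the occupation contrasts descriptive and state that they cannot be separated from calendar period.
2. Add same-day stationary readings as daily covariates where they exist (ultrafine particles, volatile organic compounds, temperature and humidity). State that this adjustment is partial: most air metrics have no stationary counterpart, and unmeasured period effects remain aliased.
3. Base exposure-biomarker conclusions on day-to-day variation within workers. This is close to the ratio and lag analyses already planned.
4. In the Discussion, qualify the statement on exposure variance: the part that lies between occupations also lies between fortnights, so a pooled slope relying on it may be confounded.

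No new data are needed. The downside is that occupation contrasts carry less weight.

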***Biomarkers of exposure***		
Transition metals (Fe, Cu, Zn, Mn, Co, Cr, Ni, Mo, Ti,V), Ba, Sb, S, Si, Al, Pb mass concentration	EBC	ICP-MS
Nanoparticles number concentration and mean hydrodynamic diameter	EBC	Nanoparticle Tracking Analyser (Malvern)
Transition metals (Fe, Cu, Zn, Mn, Co, Cr, Ni, Mo, Ti,V), Ba, Sb, Si, Al, Pb mass concentration	Urine	ICP-MS
PAH metabolites (1-hydroxypyrene)	Urine	HPLC-Fluo
***Biomarkers of effect***		
OPEA	Alveolar and bronchial part of the exhaled air	OPEA analyser + FOX colorimetric test (6 min including sampling)
Fractional Exhaled Nitric Oxide (eosinophilic inflammation)	Exhaled air	Direct-reading instrument
8-isoprostane, malondialdehyde (lipid peroxidation)	EBC	HPLC-MS/MS
8-hydroxy-2’deoxyguanosine (DNA-oxdation)	EBC	HPLC-MS/MS
NO2^−^, NO3^−^ and formate ion (nitrosant stress)	EBC	Ion-chromatography
Acetate, pyruvate, lactate, butyrate, propionate (cell metabolism)	EBC	Ion-chromatography
Malondialdehyde	Urine	HPLC-MS/MS
8-isoprostane and 8-hydroxy-2’deoxyguanosine	Urine	UPLC-MSMS
Creatinine	Urine	LC-MS/MS
Micronuclei (genotoxicity)	Buccal cells	Buccal micronuclei cytome assay

**Fig. 1 Fig1:**
[figure not shown]
Preparatory actions and measurements carried out every day for each participant during two-week prospective follow-up in the pilot study

In contrast to the pilot study, the field study will focus only on the biomarkers pre-selected in the pilot study as well as health outcomes, which will be measured only once per worker. All workers will be asked to fill in a standardized questionnaire, very similar to the questionnaire used in the pilot study. COPD diagnosis will be the principal clinical outcome. COPD assessment will be based on the 2017 update of the Global Initiative for Chronic Obstructive Lung Disease (GOLD) Guidelines [42]. Here, COPD is defined by incompletely reversible airways obstruction—that is, a ratio of the post-bronchodilator forced expiratory volume in 1 second to the forced vital capacity (FEV1/FVC ratio) of less than 70% in presence of the clinical symptoms such as dyspnea, chronic cough or sputum production. The GOLD guidelines recognize that the use of fixed FEV1/FVC ratio values will result in more frequent COPD diagnosis in elderly, and in less frequent diagnosis among adults younger than 45 years, especially for mild COPD. The lower limit of normal (LLN) values of FEV1/FVC, based on the normal distribution, classify the bottom 5% of healthy population as abnormal [42]. Considering the age-distribution within the cohort of the Parisian transport company workers [43], we will use the LLN values of FEV1/FVC as a second definition of COPD. For these LLN values, spirometric reference values determined from multi-ethnic reference values for spirometry for the 3–95-year age range (the global lung function 2012 equations) will be used [44]. The same well-trained occupational physician will perform spirometry to avoid inter-assessor differences. For every obstructive syndrome suspicion, a reversibility test by bronchodilation will be performed, to make a differential diagnosis between COPD and asthma. This and secondary health outcomes of interest are described in Table 2. The course of the typical medical check for the field study is depicted in Fig. 2. We will use the same methods for EBC, exhaled air and urine collection as those used in the pilot study and two single use cytobrushes (Cepilo cervical cell sampler, Deltalab S.L.U., Spain, cat. No. 440150) for harvesting buccal cells (< 5 minutes) (Table 3).

**Fig. 2 Fig2:**
[figure not shown]
The course of the typical medical visit in the field study. *Different steps are numbered in order of completion*

**Table 3 Tab3:** Primary and secondary health outcome definition and measurment in the field study in the Parisan subway

Outcome	Measurement method	Diagnostic criteria
Chronic Obstructive Lung Disease	Spirometry performed by the trained occupational physician with the reversibility test if necessary	Post-bronchodilator forced expiratory volume in 1 s to the forced vital capacity (FEV1/FVC ratio) of less than 70% in presence of the clinical symptoms such as dyspnea, chronic cough or sputum production
Micronuclei frequency	Micronuclei counting (per 1000 cells (‰)) according to the standardized protocol (Buccal Cell Micronuclei Assay)	The individual measured values will be interpreted using a frequency diagram of micronuclei versus age in the healthy unexposed population (51). Values above reference values for a given age will be considered an early signal of the effect of genotoxic exposure
Asthma	Self-administered questionnaire	Being on treatment for asthma or at least one of the symptoms suggestive of asthma (asthma attack(s), wheezing in the chest, difficulty in breathing, attack of breathlessness) in the past 12 months
Chronic bronchitis	Self-administered questionnaire	Productive cough for at least 3 consecutive months per year and for at least 2 consecutive years or when the diagnosis has been confirmed by a physician
Emphysema	Self-administered questionnaire	Diagnosis has been confirmed by a physician
Active allergic rhinitis	Self-administered questionnaire	Symptomatic allergic rhinitis (sneezing or a runny or stuffy nose without having a cold or the flu) and under treatment during the last 12 months
Eczema	Self-administered questionnaire	Eczema diagnosis and/or treatment in the past 12 months
Atopy	Immediate reading allergic skin tests by the prick-test technique for 12 most common pneumallergens	The test results will be read by the occupational physician and considered positive if the diameter of the papule formed is greater than or equal to 3 mm and at least equal to half of the papule of the positive control (histamine)

